## 1. SIGNIFICANCE AND BACKGROUND:

The proposed research, building on an ongoing AHRQ-funded research project to prevent pediatric diagnostic errors in primary care (R01HS023608) and using a prospective, cluster-randomized, stepped wedge design, will investigate whether 1) a quality improvement collaborative (QIC) intervention without subspecialist involvement, 2) a QIC with subspecialists and primary care physicians (PCPs) mutually engaged, and/or 3) a hub and spoke co-diagnosis, co-management model where PCPs diagnose and manage pediatric hypertension (HTN) with a supporting subspecialist advisor, reduce errors in pediatric HTN diagnosis and management compared to each other and usual care. We will also investigate time to HTN diagnosis and management, PCP and subspecialist satisfaction, and correct blood pressure (BP) measurement procedures. This project will be carried out in a national group of primary care practices in urban, rural and suburban locations. This approach, integrating PCP and subspecialty care physicians, could serve as a model across the spectrum of pediatric chronic diseases.

### 1.1. Summary of Significance

Pediatric HTN causes appreciable morbidity in pediatric patients and errors in diagnosis and management are frequent and understudied, jeopardizing pediatric safety in ambulatory settings. Additionally, the gap between the number of pediatric subspecialist providers and the number needed for patient care continues to widen, and it is unclear how to best reduce burden on subspecialists, improve PCP and subspecialist communication, and improve patient outcomes. This research team, with significant experience researching ambulatory pediatric safety, conducting QICs and HTN interventions, identified six large pediatric practice groups in rural, suburban and urban locations that are committed to reducing preventable HTN patient harm, to testing the effectiveness of a QIC to improve PCP HTN diagnosis and management, and to a hub and spoke HTN co-diagnosis and co-management model. The effect demonstrated by this project using a rigorous research design and the new 2017 pediatric HTN guidelines, will motivate pediatric clinics across the country to adopt these newly-identified best practices to improve pediatric HTN care. Primary care pediatricians have an imperative to diagnose and manage HTN and elevated BP (EBP) more accurately and earlier, and to improve interactions with subspecialists to reduce the lifelong preventable harm that results from these chronic conditions. This proposal, will identify a clear implementation strategy for rigorous, evidenced-based pediatric HTN diagnosis and management, and highlight a model to increase primary and subspecialty care integration that can be reproduced across other chronic conditions.

### 1.2. Study Overview and Rationale:

This proposal aims to test whether a QIC without and with subspecialist involvement, and/or a hub and spoke PCP-subspecialty care co-diagnosis and co-management model can improve pediatric HTN care. We propose to conduct a prospective, cluster-randomized stepped wedge trial, broadening and deepening our prior work on recognition of pediatric elevated BP, which will test methodologies to ensure every pediatric patient is screened, and if EBP or HTN are present, diagnosed and managed appropriately and expeditiously. These data will inform future efforts to improve care delivery and safety for all pediatric chronic conditions, provide broad generalizability on AHRQ priority populations including rural and urban children, and generate broader data on QIC efforts aimed at pediatric HTN. Control group data from the QIC will identify incidence rates for all phases of pediatric HTN diagnosis and management errors. The proposal will also serve as a test case for whether pediatricians can manage common conditions (e.g. HTN) with a supporting

subspecialist advisor. Human subjects' protection review will be completed at Montefiore/Einstein and at each individual site as needed with assistance from the PI and the program manager.

The first step in making a HTN or EBP diagnosis is recognizing when pediatric BP is elevated. While more straightforward in adults, BP measurement in children is challenging as it requires specialized skills including 1) preparing and calming a child; 2) choosing an appropriately sized cuff, and 3) interpreting the BP based on burdensome age, sex and height tables. A study by a member of this project's leadership team demonstrated that 39% of children have elevated BP readings at pediatric visits but 87% of these elevations are not recognized by the PCP. Other studies found that 74% of children with HTN or EBP were misdiagnosed by pediatricians, and that 47% of pediatricians classified one or more elevated BP readings as normal. Misdiagnosed pediatric HTN has appreciable cardiovascular consequences for children including increased rates of progression towards insulin resistance, atherosclerosis and metabolic syndrome. Pediatric HTN is also associated with increased risk of adult HTN. Additionally, studies demonstrate EBP and HTN cause irreversible cardiovascular damage in children suggesting diagnosis and management occur too late in the disease process. Guidelines for pediatric HTN and EBP were recently updated. To our knowledge this is the first proposal which will implement the new HTN guidelines and improve pediatric HTN diagnosis and management.

The number of pediatric ambulatory care visits resulting in a subspecialist referral more than doubled in 10 years to 10.5 million annually in 2009, suggesting an increasing need for pediatric PCP and subspecialty care integration. Unfortunately, pediatric subspecialists are often maldistributed and frequently have long waits for visits, even in urban areas with higher subspecialist concentration. Additionally, the increasing sub-specialization of pediatric care due to increasing technology and medico-legal concerns may unintentionally reduce the scope of pediatric PCP practice, and overburden subspecialists with patients not suited for their clinics. When children do access care, communication is often poor: PCPs report not being able to access subspecialist plans of care, parents are expected to communicate between medical disciplines, and children are left with incompletely addressed medical sequelae. Almost two-thirds of PCPs report being dissatisfied with the referral process, more than two-thirds of subspecialists report receiving no information from the PCP, and one-quarter of PCPs receive no subspecialist feedback after four weeks. Families similarly identify multiple obstacles to excellent subspecialty care. As the mismatch between pediatric subspecialist need and pediatric subspecialist availability grows, children with chronic conditions will be increasingly subjected to suboptimal medical care and health outcomes.

While adult patients with HTN are commonly managed by PCPs, pediatric HTN patients are commonly referred to pediatric nephrologists and/or cardiologists, despite the fact that 66%-80% of pediatric patients can likely be managed using evidenced-based algorithms in a primary care setting. The majority of pediatric HTN subspecialists agree that PCPs can make the diagnosis of HTN independently, and cite over-referral of patients due to inaccurate BP readings as a problem in their clinics. Given the harmful sequelae, it is essential that we improve PCP and subspecialist care integration for pediatric chronic conditions like HTN.

One possible solution to the pressing need for pediatric subspecialist care and improved PCP and subspecialist care integration is a 'hub and spoke' co-diagnosis and co-management model, where one subspecialist advises and consults with multiple PCPs. In the hub and spoke model, the patient is seen by a PCP in the primary care setting, reducing wait times and transportation costs, especially for rural patients. The PCP is supported by a subspecialist who can help develop algorithms for care before patient encounters, aid the PCP with unexpected findings and questions as needed. The hub and spoke model was successfully utilized for treatment of patients with *human immunodeficiency virus* (HIV) at the PI's current institution. Researchers found no difference in HIV patient outcomes comparing those treated at a subspecialist HIV clinic and those treated by a PCP with HIV subspecialist support. The hub and spoke model has also been successfully

employed to teach pediatric quality improvement. A co-investigator on this grant, [name], employed the hub and spoke model to improve PCP management of patients with sickle cell disease, another pediatric chronic condition. Other examples of pediatric hub and spoke care exist and suggest benefit, although small sample sizes, short follow-up times, and lack of rigorous statistical testing reduces the generalizability of these preliminary works. To clarify, a hub and spoke model differs from telemedicine because its goal is for the PCP to become increasingly comfortable with diagnosing and managing patients with a given chronic condition, not just improving access to subspecialists who still require the time and availability to meet with a patient via a telemedicine technology platform. Many PCPs support increasing autonomy with chronic care conditions, including HTN, and the hub and spoke model has the potential to 1) free subspecialists to see more complex patients, 2) allow PCPs to deliver guideline-based and equally efficacious care, and 3) improve patient safety by providing expeditious chronic care management.

One of the central challenges to diagnosing pediatric patients with hypertension is the need for three sequential office visits with elevated BP measurements documented to confirm that the BP elevations are sustained. Many patients do not return for second or third BP measurements because they are asymptomatic. In the first year of the BP-CATCH study, we observed this problem first hand as over 75% of patients did not return on time for their second or third BP measurement. This problem is exacerbated by the COVID-19 pandemic and the resulting telemedicine environment, as it becomes even harder for patients to feel safe to return to a clinical site solely for BP measurements.

One potential solution to this problem is confirm the blood pressure elevations in a home environment with home blood pressure monitoring (HBPM). This approach minimizes the need for patients to return for an in-person repeat and confirmatory BP measurement and is family-centered by acknowledging hesitancy to return to clinical environments during COVID-19. HBPM uses an automated BP device to measure resting out of office blood pressure in a standard way. Patients obtain three BP measurements each morning and three each evening for seven days. These measurements are then averaged to help determine if the patient has consistently elevated BPs which would warrant further evaluation and treatment. HBPM is not endorsed as a tool for the diagnosis of hypertension in the current evidenced based guidelines for pediatric hypertension due to insufficient evidence, but it is recommended as an adjunct for out of office management of children with an established diagnosis. Notably HBPM is included in the European pediatric hypertension guidelines as an adjunct for diagnosis, and is a guideline-based tool often used by adult practitioners to aid in the diagnosis and management of adult hypertension.

HBPM offers patients and providers an opportunity to continue to provide preventive care in an innovative, family-centered way during telemedicine visits or during any situation which makes in-person clinic visits challenging. Children and adolescents with elevated blood pressure could perform out-of-office blood pressure measurements via HBPM to determine if their BP elevations are sustained and warrant further evaluation. This strategy could bridge the gap of missed primary care prevention and could facilitate the diagnosis of this condition that affects 3-4 out of every 100 children in the US. Before broad implementation of this strategy, we need to understand how HBPM correlates with in-office manual BP measurements.

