#### 4. Pediatric HTN Outcome Measures:

The research team has developed clearly defined primary and secondary outcome measures for pediatric HTN diagnosis and management errors, and has experience using evidence-based tools for their improvement. All outcome measures are described in Table 2. **Error! Reference source not found.** These measures will be compared between usual care, QIC without subspecialist involvement, QIC with subspecialist involvement, and hub and spoke QIC. The primary outcome is pediatric HTN or EBP diagnosis and management errors, defined as the number of patients with an elevated systolic or diastolic BP for age, sex and height (defined as  $\geq 90^{\text{th}}$  percentile for age, sex and height or  $>120/80$ , whichever is lower, in  $\geq 3$  year old patients) who did not have all correct diagnostic

and management decisions completed per 100 patients with an elevated BP measured across all 3 intervention conditions versus usual care (control) condition. Each practice site will identify the first 10 patients seen in their site monthly with an elevated BP and then evaluate those patients following the elevated BP to confirm correct HTN and EBP diagnosis and management steps. During the baseline period, this number will be 17 patients per month for 3 months, in order to provide an adequate baseline sample for practices to begin changing their practice. For example, if a patient already had one elevated BP reading in the Stage 1 HTN range and then presented for care, the practice site would record if they 1) received a repeat BP measurement in 1-2 weeks, 2) four extremity BP measurements and 3) a scheduled appointment for a repeat BP measurement in 3 months, etc... Similarly, if a patient already had 3 BPs in the Stage 1 HTN range and then presented to the practice site, this measure would track whether they received 1) all appropriate laboratory testing, 2) a subspecialist referral, and if diagnosed with HTN, 3) management with a recommended antihypertensive medication. In this way practice sites will be able to feasibly collect data, receive real-time and actionable data feedback, and work to reduce harmful errors. We acknowledge that HTN error measurement in the control period may introduce an intervention effect, but we have no reason to believe this effect will be different between the intervention and control practices.

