#### Exclusion Criteria for Initial Visit:

- Prior hypertension/elevated BP diagnosis. NOTE: Patient can have prior elevated BP measurements as long as no diagnosis has been made
- $\text{BP} \geq 95^{\text{th}}$  percentile + 30mm or  $>180/120$  or symptomatic patient
- Prior diagnosis of congenital heart disease, chronic kidney disease, urologic disease (e.g. posterior urethral valve, vesicoureteral reflux) or organ transplant,
- Previously included in BP-CATCH data entry
- Acute care visit (e.g., fever, viral illness, asthma attack, pain in any body part, etc.)

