3. MRN: \_\_\_\_\_  
4. Date of Birth (MM/DD/YYYY): \_\_/\_\_/\_\_\_\_  
5. Patient's chart FIRST reviewed on (MM/DD/YYYY): \_\_/\_\_/\_\_\_\_  
6. REDCap Record ID: \_\_\_\_\_

**EXCLUDE Patients:** not at healthcare maintenance visits or non-acute care visits, prior hypertension/elevated BP diagnosis, prior diagnosis of congenital heart disease, Chronic Kidney Disease, urologic disease, or organ transplant, BP ≥ 95th percentile + 30mm or >180/120 or symptomatic patient, previously included in BP-CATCH data entry

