**B. How Many Elevated BPs at Unique Visits in the Last 24 Months?**

1. In the last 24 months, at healthcare maintenance and/or non-acute care visits, how many elevated BPs did the patient have at unique visits? Please count total number of unique visits with abnormal BPs and no normal BPs at those visits in the last 24 months at a healthcare maintenance or non-acute care visits and check appropriate box

**Note:** A patient may also have one or more normal BPs at separate unique visits in the last 24 months at healthcare maintenance or non-acute care visits and be included.

- ☐ This visit is their **First elevated BP** [Go to Section C]  
☐ This visit is their **Second elevated BP** [Go to Section D]  
☐ This visit is their **Third elevated BP** [Go to Section E]  
☐ This visit is their **Fourth or more elevated BPs** [Go to Section E]  
☐ This visit is their first visit to this clinic or in our EHR. Therefore, this visit is their **First elevated BP** [Go to Section C]

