6a. Did the patient have BP in Stage II Hypertension range ( $\geq 95$ th+12mm to <95th+30mm; or  $\geq 140/90$  to <180/120) at the prior visit?

☐ Yes [Go to 6b] ☐ No [Go to 7]

6b. Did the provider document a diagnosis of 'Stage II Hypertension' in notes, billing or problem lists at this visit?

☐ Yes [Go to Section F] ☐ No [Go to Section F]

7. Did the patient have BP in Stage I Hypertension range ( $\geq 95^{\text{th}}$  to  $< 95^{\text{th}} + 12\text{mm}$  or 130/80 to 139/89)?

☐ Yes [Go to 7a] ☐ No [Go to 8]

7a. Did the provider document a diagnosis of 'Stage I Hypertension' in notes, billing or problem lists at this visit?

☐ Yes [Go to Section F] ☐ No [Go to Section F]

8. Did the provider document a diagnosis of 'Elevated Blood Pressure (or BP)' in notes, billing or problem lists at this visit?

☐ Yes [Go to Section F] ☐ No [Go to Section F]

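### Control-group error rates at the diagnosis step are not incidence rates, because some entrants are sampled only if an earlier diagnosis went undocumented

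*Protocol*

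**What the plan says.** Section 1.2 gives the control data a descriptive purpose: "Control group data from the QIC will identify incidence rates for all phases of pediatric HTN diagnosis and management errors". The same section describes diagnosis as depending on "the need for three sequential office visits with elevated BP measurements documented to confirm that the BP elevations are sustained".

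The Appendix sets the entry rule. The exclusion list for the initial visit reads: "Prior hypertension/elevated BP diagnosis. NOTE: Patient can have prior elevated BP measurements as long as no diagnosis has been made". The Chart Review Tool repeats the exclusion ("prior hypertension/elevated BP diagnosis, prior diagnosis of congenital heart disease").

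Section B of the tool counts visits with elevated readings over the last 24 months. One entry category is "Fourth or more elevated BPs", and it is routed to Section E together with the third-elevation category. Depending on the reading, Section E asks "Did the provider document a diagnosis of 'Stage I Hypertension' in notes, billing or problem lists at this visit" or "Did the provider document a diagnosis of 'Elevated Blood Pressure (or BP)' in notes, billing or problem lists at this visit". Where this visit and the prior one were both in the Stage II range, it asks for a Stage II diagnosis instead. Section D already asks that Stage II question at the second elevation.

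Section 4 uses a late entrant as a worked example: "if a patient already had 3 BPs in the Stage 1 HTN range and then presented to the practice site".

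The Data and Safety Monitoring Plan adds a search rule. If none have appeared by the month's eighth chart, the site looks for at least two patients who went through work-up to the start of management.

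Section 3 says the data from November 2018 to March 2020 will be analysed and published, and Table 3 lists an epidemiology manuscript.

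**The concern.** An incidence of missed diagnosis needs children who are still at risk of the miss when the diagnosis first falls due. Here a child diagnosed on time at the third elevation leaves the frame, and a child who was missed stays in it and can be sampled at the fourth, fifth or later elevation. The Section E rate therefore pools two quantities: the miss rate at the first due visit, and the miss rate among children already missed.

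At stake is the descriptive result. A published figure for how often the diagnosis step fails under usual care would be read as a first-opportunity failure rate, which the pooled figure is not.

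**Working it through.** **Step 1. Who is selected on an earlier miss.** Reading Sections B, D and E of the tool together:

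| Entry | Visit at which the tool first asks for a diagnosis | Selected on an earlier miss? |
|---|---|---|
| First elevation | Later | No |
| Second, Stage II at this and the prior visit | This visit | No |
| Second, other | Later | No |
| Third, diagnosis not asked for at the second | This visit | No |
| Third, Stage II at both earlier elevated visits | Second elevation | Yes |
| Fourth or more | Third elevation at the latest | Yes |

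**Step 2. What is scored.** The items ask about a diagnosis documented at the current visit. For the last two rows the result is therefore the chance of a miss now, given a miss before. The earlier miss itself is not recorded as an error.

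**Step 3. Size of this route (illustration).** The protocol states no figure to reproduce. Let m be the miss rate at the first due visit, r the correlation of misses between a child's due visits, and f the share of late entrants among those pooled.

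- Miss rate given an earlier miss: [m² + r·m(1 − m)] / m = m + r(1 − m)
- Excess of the pooled rate over m, with two due visits: f × r × (1 − m)

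Inputs:
- m = 0.73, the usual-care error rate in Section 6.3. It is borrowed, since it is a planning figure and not a first-due miss rate.
- r = 0 to 0.5, assumed. Section 6.3 uses 0.5 for charts within a site and month, so it serves here only as an upper end.
- f is not given. If a child is equally likely to be sampled at either of two due visits, f = m / (1 + m) = 0.73 / 1.73 = 0.422.

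| r | Miss rate, late entrants | Excess, two due visits | Excess, three due visits |
|---|---|---|---|
| 0 | 73.0% | 0 | 0 |
| 0.1 | 75.7% | 0.422 × 0.027 = 1.1 points | 75.1 − 73.0 = 2.1 points |
| 0.3 | 81.1% | 0.422 × 0.081 = 3.4 points | 78.7 − 73.0 = 5.7 points |
| 0.5 | 86.5% | 0.422 × 0.135 = 5.7 points | 82.0 − 73.0 = 9.0 points |

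The last column takes each child's miss probability as beta-distributed. Setting f at 25% to 50% instead gives 0.7 to 1.4 points at r = 0.1 and 3.4 to 6.8 points at r = 0.5. With two due visits and r = 0.5, the excess is 8.3 points at m = 0.50 (58.3 − 50.0) and 3.0 points at m = 0.87 (90.0 − 87.0).

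**Step 4. The opposing route.** Suppose a site-month has three charts at the diagnosis step with 73% missed, and the search adds two charts scored as diagnosed. The rate becomes 3 × 0.73 / 5 = 43.8%, about 29 points lower. These counts are assumed too. They show only that the search rule can outweigh the excess in Step 3.

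**The case against.** The strongest reply is that the word incidence appears in a rationale section, while the outcome in Section 4 is openly a proportion per 100 patients with an elevated reading. The entry rule is stated plainly, the elevation number is recorded, and splitting a descriptive rate by a recorded item could be left to a statistical analysis plan. All of that is fair and keeps the point small. It does not make the stated purpose fit the frame: both are in the protocol, and as written they disagree.

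A second reply is that Section 1.2 speaks of sequential elevated visits, whereas Section B counts elevated visits over 24 months and allows normal visits in between. A fourth-or-more child with interrupted elevations need not have been due a diagnosis under Section 1.2. This stands, so the selection argument rests on the tool's logic, which asks for a diagnosis at the third counted elevation.

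Several stronger readings are tempting and are not supported:

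- *The control rates will be too high.* Not established. The excess vanishes if misses are independent, and the search rule pulls the other way.
- *Earlier misses are counted a second time.* They are not. The form scores the current visit, and a child already included cannot re-enter.
- *Work-up and management rates are inflated as well.* Not shown. Section F is reached whether or not a diagnosis was documented, and it asks which laboratory results have come back since the second or third elevated reading. A late entrant has had longer to accumulate them.
- *The randomised comparison is biased.* Not shown. The same entry rule applies under every condition.

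**Conclusion.** The point holds in a limited form. At the diagnosis step, the control data give a mixture of first-due error rates and rates conditional on an earlier undocumented diagnosis, so they do not give an incidence. That conclusion follows from the entry rule and the form's routing alone.

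The size is an illustration. This route adds nothing if misses are independent and about 1 to 6 points for correlations of 0.1 to 0.5, taking a 73% miss rate and two due visits. A third due visit takes the upper end to 9 points. The documents give neither the share of late entrants nor the correlation between repeat visits. Because of the search rule, the sign of the net error is open. The consequence is confined to the descriptive control rates, so this is a minor but worthwhile correction.

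**What to change.** 1. Report the control-period diagnosis error rate among children first reaching the visit where the tool asks for the diagnosis: the second elevation for repeated Stage II readings, otherwise the third. Include children who enter earlier and reach that visit on follow-up. This adopts the tool's timing for analysis only and takes no position on when a diagnosis should be made.
2. Report later entrants, identified from item 1 of Section B, separately as persisting missed diagnoses.
3. Leave out charts added under the search rule, or report them separately.
4. In Section 1.2, replace the reference to incidence with error rates in children without a prior diagnosis. This rewording must accompany the split, since on its own it leaves the mixture in place.

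Cost: one sentence and a split on an item already collected, with fewer charts in the first-due estimate. Two practical points need care. Searched-for charts must be identifiable, and the tool as shown has no field for this. For a child entering at the third elevation, Section E records whether the prior visit was Stage II but not the visit before it. The early-due Stage II group therefore needs a look back in the chart, or can be approximated by showing children with a yes to item 6a of Section E separately.
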